# Laparoscopic roux-en-Y gastric bypass versus sleeve gastrectomy for teenagers with severe obesity - TEEN-BEST: study protocol of a multicenter randomized controlled trial

**DOI:** 10.1186/s12893-020-00778-9

**Published:** 2020-06-03

**Keywords:** Adolescents, Bariatric surgery, Sleeve gastrectomy, Roux-en-Y gastric bypass, Severe obesity

## Abstract

**Background:**

Recent data support the use of bariatric surgery in adolescents with severe obesity following unsuccessful non-surgical treatments. Sleeve gastrectomy (SG) and Roux-en-Y gastric bypass (RYGB) have demonstrated reasonably similar weight loss and reduction of obesity related comorbidities in randomized trials in adults. SG has internationally become the most commonly used procedure in adolescents, yet long-term outcome data are lacking. No randomized controlled trial comparing SG and RYGB has been performed in adolescents.

**Objective:**

Determine whether SG is non-inferior to RYGB in terms of total body weight (TBW) loss in adolescents with severe obesity.

**Methods:**

A multicenter randomized controlled non-inferiority trial. Two hundred sixty-four adolescents aged 13–17 (Tanner stage ≥IV) with severe obesity (corrected for age and sex) will be included. Adolescents agreeing to participate will be randomized to either RYGB or SG. The primary outcome is the proportion of participants achieving 20% TBW loss at 3 years postoperatively. Secondary outcomes include (i) change in body weight, body mass index (BMI) and BMI standard deviation score, (ii) incidence of adverse health events and need for additional surgical intervention, (iii) resolution of obesity-related comorbidities, (iv) prevalence of cardio metabolic risk factor measures, (v) bone health measures and incidence of bone fractures, (vi) quality of life including psychosocial health, patient satisfaction and educational attainment and (vii) body composition. Follow-up will extend into the long term.

**Results:**

Not applicable.

**Discussion:**

This study will, to our knowledge, be the first randomized controlled trial comparing SG and RYGB in adolescents with severe obesity.

**Trial registration:**

The trial is registered at the Netherlands Trial Register on July 26th, 2018 – NTR7191 - https://www.trialregister.nl/trial/7191 (protocol version 5.0 – February 3th 2020).

## Background

The prevalence of overweight and obesity in adults is still increasing worldwide. Parallel to this, the prevalence of overweight and obesity in children has increased by almost 50% between 1980 and 2013 [1]. The majority of children with obesity will remain affected into their adult life [2], especially those with severe obesity post-pubertally [3].

Obesity is a chronic disease associated with several comorbidities including Type 2 diabetes (T2D), cardiovascular disease (including hypertension and dyslipidemia), musculoskeletal disorders and some cancers [4]. Correlated to the increase in prevalence of childhood obesity, an alarming shift in the onset of these obesity related comorbidities towards childhood has been noted, particularly for T2D [1, 5–10]. The timeframe between the onset of T2D and the requirement of insulin therapy is shorter in adolescents than in adults, with medical treatments failing earlier [7, 8]. Additionally, other comorbidities including metabolic disturbances also develop earlier in life [10]. All these factors contribute to a poor prognosis in adolescents with severe obesity, in whom studies have indicated a reduction in life expectancy of almost 20 years [5, 11, 12].

The standard treatment for obesity in children consists of multimodal lifestyle intervention programs, delivered by an expert multidisciplinary team focusing on eating patterns, exercise and behavior. An updated Cochrane Review meta-analyzed 37 studies, including a total of 27,946 children, concluded that there is strong evidence for the beneficial effects of multimodal lifestyle intervention programs for childhood obesity. Results included a mean reduction of 0.15 kg per meter squared (kg/m^2^) in body mass index (BMI). However, the reduction in the adolescent group (aged 13–18 years) was only 0.09 kg/m^2^ [13]. A study from the Netherlands showed that a multimodal lifestyle intervention program resulted in significant weight loss and improvement of cardiovascular risk parameters in children with overweight, obesity and severe obesity, all to a similar degree. In children with severe obesity a decrease in BMI z-score of − 0.23 ± 0.32 (*p* = 0.01) was observed after 2 years. Overall, 68% percent of the participants achieved a successful weight reduction, defined as 10% weight loss at 24 months follow-up [14]. However, despite these promising results, as much as one quarter do not experience weight reduction, which mainly applies to adolescents [14, 15]. Lifestyle intervention is thus not a solution for a subgroup of adolescents with severe obesity, whereas comorbidity is high in this group, urging for other intervention possibilities. Bariatric surgery should be studied as an option.

A recent systematic review of medium- and long-term outcomes (minimum three-year follow-up) of bariatric surgery including 950 adolescents with severe obesity, aged twelve to nineteen years, showed an average decrease in BMI of 13.3 kg/m^2^. Resolution of T2D/insulin resistance, hypertension and dyslipidemia occurred in 69.9, 61.6 and 57.1% of patients respectively. The rate of reoperation was 9.6%, mostly because of postoperative complications and suboptimal weight loss [16]. Olbers et al. reported similar weight loss results over 5 years among adolescents and adults who received a Roux-en-Y gastric bypass (RYGB), with a mean BMI-reduction of 13.1 kg/m^2^ in the adolescent intervention group. Notably, the control group of adolescents, who attended multimodal lifestyle intervention programs, experienced a mean increase in BMI of 3.3 kg/m^2^ across the five-year study period. Regarding comorbidities among adolescents who received the RYGB, resolution of hypertension was seen in 100%, resolution of dyslipidemia in 82.7% and complete resolution of T2D and disturbed glucose homeostasis in 100% (*n* = 3) and 85.7%, respectively [17]. In recent years, Inge et al. have published three-year outcomes from the Teenage Longitudinal Assessment of Bariatric Surgery (Teen-LABS) prospective longitudinal study including adolescents undergoing sleeve gastrectomy (SG) and RYGB. This study showed a mean three-year BMI reduction of 15 kg/m^2^ after RYGB and 13 kg/m^2^ after SG. Furthermore, significant improvements were observed in weight related quality of life and cardio-metabolic health (95% remission of T2D, 86% remission of abnormal kidney function, 74% remission of elevated blood pressure, 76% remission of prediabetes and 66% remission of dyslipidemia). This study suggested that risks associated with the procedures may be more prevalent after RYGB and included specific micronutrient deficiencies and the need for additional abdominal procedures [18]. The Teen-LABS group subsequently published 5-year outcomes after RYGB in comparison to adults in a similar study, LABS (Longitudinal Assessment of Bariatric Surgery). This confirmed similar weight loss outcomes between adolescents and adults, but a more favorable T2D and hypertension outcome in adolescents, supporting the case for early intervention [19].

The rates of remission of comorbidities after bariatric surgery observed in each of the previous mentioned studies were higher than those reported in adults, suggesting that adolescents may have a greater potential than adults for reversal of the cardio-metabolic consequences of obesity [17–19]. In addition, Panunzi et al. showed in the Swedish Obese Subjects study of adult patients that when T2D diagnosis was new (< 1 year) bariatric surgery resulted in > 90% remission, whereas a diagnosis of T2D > 4 years ago resulted in less than 40% remission [20]. Therefore, delay of surgical treatment until adulthood is negatively associated with the reduction of several comorbidities, cardiovascular risk profile and premature death.

In short, among adolescents with severe obesity who do not respond sufficiently to multimodal lifestyle interventions, bariatric surgery is a viable option. Although both SG and RYGB showed successful weight loss and reduction of obesity related comorbidities in adolescents thus far, long-term outcome data of SG in adolescents has been limited and, to date, no randomized controlled trial (RCT) has been performed in adolescents directly comparing these two procedures. This clear knowledge gap hampers optimal procedure selection for adolescents and thus prevents evidence-based recommendation to eligible adolescents. Therefore, we propose an RCT comparing SG with RYGB in adolescents with severe obesity.

## Methods/design

### Hypothesis

SG in combination with lifestyle intervention is non-inferior to RYGB in combination with lifestyle intervention in terms of proportion of participants achieving a total body weight (TBW) loss of at least 20% at 3 years, with an equivalent or lower rate of complications.

### Objective

The main objective of this trial is to obtain level one evidence regarding differences in clinical outcomes between RYGB and SG (both performed as add on to lifestyle intervention) in adolescents with severe obesity. By assessing efficacy and safety we aim to provide guidance regarding procedure choice based on reliable risk/benefit data overall as well as in subgroups.

### Trial design

This trial is designed as a non-inferiority, parallel, international multicenter, randomized controlled trial, comparing two bariatric surgeries (RYGB and SG) in adolescents with morbid obesity. The TEEN-BEST flow-chart, including the participant timeline, is shown in Fig. 1.

**Fig. 1 Fig1:**
[figure not shown]
TEEN-BEST flowchart and participant timeline. RYGB = Roux-en-Y Gastric Bypass, SG = Sleeve Gastrectomy, DEXA-scan = Dual-energy X-ray Absorptiometry scan

The trial consists of two phases. Phase 1 will be an internal pilot of twenty patients at each of the two initiating surgical sites (10 + 10 SG and 10 + 10 RYGB in total) to establish feasibility. The methods of recruitment and informed consent will be refined over this period. Phase 2 will be the full multicenter RCT. Patients will be recruited starting in May 2020 until May 2023. Follow-up within the RCT will be planned for a minimum of 5 years.

A matched group, identified from historical data in the multimodal lifestyle intervention program (COACH) of Maastricht University Medical Center, will be used as a non-surgical comparator to the bariatric procedures.

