### Study setting

This study will initially be conducted at two surgical sites (a non-academic Dutch center and an academic Swedish center), with the potential to recruit additional sites after successful initiation. All surgical centers will collaborate with a child obesity center, which will initially be three sites (one academic and one non-academic Dutch center and one academic Swedish center). The list of study sites can be obtained from the corresponding author ([contact]).

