#### Secondary outcome measures

To compare outcomes between SG and RYGB. In addition, a historical cohort of adolescents who participated in a lifestyle intervention program only will be compared to both study arms on these secondary objectives (except for (ii) and (vii)).
(i)BMI, BMI standard deviation score and TBW loss [1, 3 and 5 years after the bariatric surgery]: weight loss is measured in kilogram and as percentage TBW loss;(ii)Adverse health events [1, 3 and 5 years after the bariatric surgery]: including complications (within 30 days and beyond 30 days of bariatric procedure) and the need for re-operation. Complications will be scored according to the Clavien Dindo Classification [25];(iii)Resolution of co-morbidities [1, 3 and 5 years after the bariatric surgery]: blood pressure (systolic and diastolic), lipid profile (HDL, LDL, TG), glucose control (HbA1c, fasting blood glucose level, fasting insulin, HOMA-IR), Obstructive Sleep Apnea (OSA) (Epworth sleepiness scale), kidney function (Glomerular Filtration Rate, microalbuminuria, creatinine), liver disease (i.e. non-alcoholic fatty liver disease) (alkaline phosphatase, gamma glutamyl transpeptidase, aspartate-aminotransferase, alanine-aminotransferase, bilirubin, ultrasound (baseline, 3 and 5 years post-surgery) and decrease/change in medication for each of the co-morbidities;(iv)Resolution of OSA, T2D and pre-diabetes, hypertension, dyslipidemia, deranged liver function [1, 3 and 5 years after the bariatric surgery];(v)Prevalence of cardio-metabolic risk factor measures [1, 3 and 5 years after the bariatric surgery];(vi)Routine post-bariatric surgery nutritional blood tests at each assessment [1, 3 and 5 years after the bariatric surgery]: including full blood count, electrolytes, creatinine, fasting glucose, fasting insulin, HbA1c, liver parameters and function tests, iron, ferritin, vitamin B12, thiamine, folate/red cell folate, lipid profile, 25-hydroxyvitamin D, calcium and parathyroid hormone;(vii)Bone health measures and the incidence of bone fractures [baseline and at 2 and 5 years after the bariatric surgery]: bone mineral density (DEXA-scan), osteocalcin, PINP, CTX and bone-specific alkaline phosphatase;(viii)Generic and obesity-specific health-related quality of life [1, 3 and 5 years after the bariatric surgery]: IWQOL-Lite, RAND-36, Kidscreen-27;(ix)Psychosocial health measures and educational attainment [1, 3 and 5 years after the bariatric surgery]: education, depression (Beck Depression Inventory), anxiety (Beck Anxiety Inventory), self-esteem (Kidscreen-27, IWQOL-Lite), attention deficit hyperactivity disorder (AVL);(x)Patient satisfaction [1, 3 and 5 years after the bariatric surgery]: single question scale 1–10 and net promotor score;(xi)Body composition [1, 3 and 5 years after the bariatric surgery]: DEXA-scan.

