### Randomization

Randomization will be performed by the coordinating investigator after trial eligibility and informed consent to participate in the trial have been confirmed. Randomization will be performed using a computerized randomization program (Research Manager), which will produce unchangeable computer-generated numbers. Randomization will be stratified according to centers in order to ensure balanced groups. Randomization will be on a 1:1 basis using block sizes of 6–8 participants.

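### The matched lifestyle-only group comes from one Dutch programme, so for Swedish participants the secondary surgery-versus-lifestyle contrasts confound surgery with country and programme

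*Protocol article*

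**What the plan says.** Four parts of the protocol article bear on this point.

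- **Trial design (text under Fig. 1).** The matched group is "identified from historical data in the multimodal lifestyle intervention program (COACH) of Maastricht University Medical Center" and "will be used as a non-surgical comparator to the bariatric procedures". No other lifestyle-only source is named. That Maastricht is in the Netherlands is common geography; the article does not say so in words.
- **Study setting.** The trial opens at "two surgical sites (a non-academic Dutch center and an academic Swedish center"), with more sites possible later. The child obesity centres feeding it are initially "one academic and one non-academic Dutch center and one academic Swedish center".
- **Randomization.** Allocation is 1:1, and "Randomization will be stratified according to centers in order to ensure balanced groups". Phase 1 is an "internal pilot of twenty patients at each of the two initiating surgical sites", split equally between SG and RYGB.
- **Secondary outcome measures.** Here "a historical cohort of adolescents who participated in a lifestyle intervention program only will be compared to both study arms on these secondary objectives". Only item (ii), adverse health events, and item (vii), bone health, are exempt. Change in medication (iii), quality of life (viii), and psychosocial health with educational attainment (ix) all stay in.

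Nothing in the article limits this comparison to Dutch participants.

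**The concern.** Matching can balance a characteristic only where the comparator pool contains people who have it. Here every comparator comes from one programme in one country, so the Swedish part of each surgical arm has no counterpart. For those participants, a difference from the lifestyle group could come from surgery, from country, from the lifestyle programme, or from a mixture, and the data cannot separate them.

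This matters because it is the only comparison with non-surgical care in the plan. Several retained outcomes plausibly depend on national setting: educational attainment on the school system, medication change on local prescribing, and questionnaire scores on language and culture. A larger sample does not shrink a bias of this kind, and the planned 95% confidence intervals would not show it. Calling the group matched could lead a reader to think country has been dealt with.

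**Working it through.** **1. The plan's own figure.** The article gives no sample size for the lifestyle contrast. The only stated size is 132 per arm for SG versus RYGB. With 70% success in both arms, margin 0.20, one-sided alpha 0.025 and 90% power:

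n = (1.960 + 1.282)² × 2 × 0.70 × 0.30 / 0.20² = 110.3, so 111 evaluable per arm.

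Allowing for 15% dropout, 111 / 0.85 = 130.6, so 131, against 132 stated. The figure reproduces. In the other direction, 132 × 0.85 = 112 evaluable, with power 0.904. The 112 is used below.

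**2. Overlap on country.** The Swedish site supplies 20 of the 40 phase 1 patients (50%). Because randomisation is 1:1 within centre, both arms contain Swedish participants. The number of Swedish lifestyle-only comparators in the named source is 0. No choice of matching variables changes that.

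**3. Illustrative size of the bias.** For a crude all-site difference, bias = Swedish share × country/programme difference. Assumptions not in the document: the Swedish share after the pilot, the country/programme difference, 112 matched controls, an outcome scaled to SD 1, independent groups, and no true surgery effect.

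SE = √(1/112 + 1/112) = 0.134 SD. The last column is the rejection probability of a two-sided 5% z-test.

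| Swedish share | Difference (SD) | Bias (SD) | Rejects |
|---|---|---|---|
| 0.3 | 0.2 | 0.06 | 7% |
| 0.5 | 0.3 | 0.15 | 20% |
| 0.5 | 0.5 | 0.25 | 46% |

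For a proportion, a country/programme difference of 5 to 20 percentage points gives a bias of 1.25 to 5 points at a share of 25%, 2.5 to 10 points at 50%, and 3.75 to 15 points at 75%.

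**4. Precision of a Dutch-site contrast.** With half of each arm Swedish, 56 surgical patients per arm face 112 controls: SE = √(1/56 + 1/112) = 0.164 SD, or 1.22 times 0.134.

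**5. Bias against variance.** Root-mean-square error = √(bias² + SE²), taking the Dutch-site contrast as free of this bias.

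- Share 0.3, difference 0.2 SD: all-site √(0.06² + 0.134²) = 0.147; Dutch-site (78 v 112) √(1/78 + 1/112) = 0.147.
- Share 0.5, difference 0.2 SD: all-site √(0.10² + 0.134²) = 0.167; Dutch-site 0.164.

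At a difference of 0.2 SD the two are about equal. Above it the Dutch-site version gains on this measure; below it the all-site version does.

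**The case against.** **No figure in the article measures a country effect.** This stands. A reader might infer one from the Background, where a Dutch lifestyle study reports a BMI z-score change of −0.23 at 2 years in severe obesity and a lifestyle control group elsewhere gains 3.3 kg/m² over five years. The inference fails. One result is an age-corrected score and the other raw BMI, the follow-up differs, one group is children and the other adolescents, and the country of the second group is not stated.

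**The share-times-difference formula describes a crude difference in levels.** This largely stands. The data analysis section models continuous outcomes measured repeatedly, including quality-of-life scores, with baseline and follow-up jointly. If that model is also used here, stable level differences between countries may drop out. Differences in trajectory would remain, and so would educational attainment, which depends on the school system. Reading every all-site estimate as biased by the full product goes too far.

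**Details of matching belong in the full protocol or analysis plan.** This is true of the matching variables and of any analysis by country. It does not meet the point, because the source of the comparator is not left open, and no matching variable supplies Swedish patients.

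**A Dutch-site analysis is not clean either.** This stands. There are two Dutch child obesity centres, the consent section allows identification by outside pediatricians, and the group is historical. Restriction removes country but not all programme or period confounding.

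**The stakes are limited.** This stands too. The hypothesis, primary outcome, sample size and randomisation all concern SG versus RYGB.

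**Conclusion.** The concern holds as a limit on the secondary surgery-versus-lifestyle contrasts. The comparator source is a stated design choice, it contains no Swedish patient, and matching therefore cannot balance country. For Swedish participants surgery is confounded with country and programme.

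The size and direction of the bias are unknown. The rejection rates of 7% to 46% rest wholly on assumed inputs and on a crude comparison of levels; they show what could happen and are not estimates for this trial. Educational attainment is the clearest exposed outcome. For weight, the surgical effect is probably large enough to dominate.

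Two stronger readings are tempting but unsupported. One is that the trial's main conclusion is compromised: it is not, because SG and RYGB are compared by randomisation stratified by centre. The other is that the Dutch-only version must be the leading analysis: the near-equal root-mean-square errors at 0.2 SD show that this is a bias–variance choice. What the documents support is reporting both and labelling them plainly.

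**What to change.** In the Trial design and Secondary outcome measures sections, and in the analysis plan:

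1. Report each surgery-versus-lifestyle contrast for Dutch-site participants, ideally those who came through COACH, against the COACH group, alongside the all-site version.
2. Label the all-site version as confounded by country, and the whole comparison as non-randomised.
3. Do not compare the educational attainment of Swedish participants with the COACH group.

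The cost is some wording and one extra set of analyses, with no new data. The Dutch-site contrast is less precise: a standard error of about 0.164 against 0.134 SD if half the participants are Swedish and there are 112 controls. Limiting it to COACH participants would reduce the numbers further. Some programme and period confounding will remain and should be stated with the results.

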### Study setting

This study will initially be conducted at two surgical sites (a non-academic Dutch center and an academic Swedish center), with the potential to recruit additional sites after successful initiation. All surgical centers will collaborate with a child obesity center, which will initially be three sites (one academic and one non-academic Dutch center and one academic Swedish center). The list of study sites can be obtained from the corresponding author ([contact]).

### Informed consent procedure

Participants will be identified by collaborators in the child obesity lifestyle programs at the participating child obesity centers or by pediatricians outside of these centers. Existing patients who have already participated for 12 months in a child obesity lifestyle program or prospective identification of new patients (minimum of 12 months in a lifestyle program) with the potential to meet eligibility will be screened for recruitment.

During a multidisciplinary meeting eligible patients will be identified. The multidisciplinary team will, as a minimum, consist of a pediatrician, a clinical psychologist, a dietician and a bariatric surgeon. Patients identified as eligible for this study during the multidisciplinary meeting will be informed by their pediatrician about the trial. All patients will receive a written information leaflet and be required to provide written informed consent. When an adolescent is interested in participating in this trial, the pediatrician will ask the individual permission for the coordinating investigator to contact them providing more information about the trial and informed consent.

Informed consent will be obtained in the outpatient clinic prior to the participant undergoing any procedure that is specifically performed for the purposes of the trial at the participating site, including the collection of identifiable participant data. This informed consent conversation will be performed with the coordinating investigator. In adolescents, aged 13–14-15 years, we will additionally obtain informed consent from either both parents or caregivers. The informed consent form of this study is attached as Supplemental Appendix File 1.

